#### 5.7.1 Prohibited Concomitant Medication/Therapy

The use of the following concomitant medications and therapies will be prohibited for 4 weeks after study drug administration. However, this does not apply when the investigator or subinvestigator determines that treatment is necessary for AE that occurs after obtaining informed consent.

- 1) Blood transfusions (including component transfusions)
- 2) Gamma globulin preparations
- 3) Systemic administration of immunosuppressive drugs (including treatments to autoimmune diseases)
- 4) Immunosuppressive therapy (including radiotherapy)
- 5) Hematopoietic agents (except for iron and vitamin preparations)
- 6) Systemic corticosteroids (excluding external agents and inhalants)
- 7) Preventive antipyretic analgesics\*
- 8) Other vaccines (excluding influenza vaccines)

Confidential

9) Other drugs used in the study

\*: The use of these drugs for prevention of fever and pain will be prohibited.

<Rationale>

- 1) to 6) These were included because these drugs/therapies may influence the immunogenicity evaluation of the study drug.
- 7) This was included because these drugs may influence the safety evaluation of the study drug.
- 8) This was included because these vaccines may influence the immunogenicity and safety evaluation of the study drug.
- 9) This was included because the safety of other drugs used in the study under development has not been established, and concomitant use of the study drug with such drugs may cause safety problems.

In addition, the use of SARS-CoV-2 vaccines (including drugs used in the study), except in this study, will be prohibited for 26 weeks after study drug administration.

<Rationale>

The use of SARS-CoV-2 vaccines (including investigational drugs), except in this study, will be prohibited for 26 weeks after study drug administration because they may influence the evaluation of long-term efficacy and safety.

## 5.7.2 Other Restrictions

During the study, the subject and partner should practice contraception with effective contraceptive methods (male contraceptive condom, oral contraceptive pill, intrauterine device, intrauterine hormone release system, bilateral tubal ligation, and vasectomy).

<Rationale>

This was included in consideration of the influence on the subject, subject's partner, fetuses, and newborn.

## 5.8 Subject Withdrawal/Discontinuation

When the subject meets the criteria described in Section 5.8.1, the investigator or subinvestigator will determine whether or not the subject should be withdrawn from the study, and if the subject is withdrawn from the study, take appropriate actions for the subject. If the subject is withdrawn from the study, the subject will not be replaced. The subject and legal representative can request

Confidential

withdrawal from the study at any time even after providing informed consent.

#### 5.8.1 Reasons for Withdrawal

- Withdrawal requested or consent withdrawn by the subject or legal representative
- AEs due to which continuing the study is considered undesirable by the investigator or subinvestigator
- Inclusion criteria not met or exclusion criteria met
- Significant deviation from the protocol
- Failure to make a visit
- Death
- Study terminated by the sponsor
- Pregnancy (subject herself)
- Otherwise considered unsuitable by the investigator or subinvestigator

#### 5.8.2 Withdrawal Procedures

If the subject is withdrawn from the study, the investigator or subinvestigator will complete the observations and examinations described in "STUDY PROCEDURES" to the extent possible, and record the results of observations up to the date of permanent discontinuation, including the date of the last dose, and the reason for withdrawal in the eCRF.

In the case of withdrawal due to an AE, the investigator or subinvestigator should follow the subject until the AE recovers or resolves to the condition before the occurrence of the AE and disappears, AE is recovering or resolving, or AE is stabilized.

#### 5.8.3 Subject Replacement

Not applicable.

#### 5.8.4 Subject Re-screening Procedures

If re-consent is obtained in writing from the subject or legal representative and eligibility is confirmed, the investigator or subinvestigator may re-enroll the subject who dropped out of the study for being determined ineligible at the time of eligibility evaluation after providing informed consent or who was withdrawn from the study during the period after randomization until study drug administration. To re-enroll such a subject, the investigator or subinvestigator will record the subject number assigned at the time of dropping out or withdrawal in the eCRF of the re-enrolled subject according to the procedures specified in Section [5.1.2](#).

### 5.9 Study Completion for Individual Subjects

If the subject completes the study at 26 weeks after study drug administration, the investigator or

Confidential

subinvestigator will complete the observations and examinations described in "STUDY PROCEDURES," and record the results of observations up to 26 weeks after study drug administration in the eCRF. If an AE persists after 26 weeks after study drug administration, the investigator or subinvestigator should follow the subject until the AE recovers or resolves to the condition before the occurrence of the AE and disappears, AE is recovering or resolving, or AE is stabilized. The outcome of the AE should be confirmed and recorded in the eCRF. Upon completion of these procedures, the study for the subject will be completed.

## 6. STUDY PROCEDURES

### 6.1 Informed Consent, Eligibility Evaluation, and Enrollment

- 1) The investigator, subinvestigator, or study staff will explain an outline of this study to the subject and legal representative and obtain written consent from the subject and, if necessary, legal representative. If the subject is aged 12 to 17 years, written consent to study participation should be obtained from the subject, depending on his/her ability of understanding. If the subject cannot sign the informed consent form (ICF) or the subject's assent is obtained orally rather than in writing, the ICF signed by the legal representative should indicate that the subject's assent has been obtained.
- 2) The investigator or subinvestigator will collect the following baseline characteristics and document them in the eCRF:
  - Birth year (western calendar) and the age at informed consent
  - Sex
  - Race, ethnicity
  - Height, body weight
  - Medical history/complications, name of diseases, and date of recovery (confirmed)
  - Self-reported SARS-CoV-2 infection history, date of onset or test, evaluation method (eg, RT-PCR, other nucleic acid detection methods, SARS-CoV-2 antigen test)
  - Presence or absence of a history of vaccination with SARS-CoV-2 vaccine, the most recent type of SARS-CoV-2 vaccines administered as well as dates of the administration

Definition of a history of SARS-CoV-2 infection reported by the subject or legal representative (self-reported SARS-CoV-2 infection history)

A subject with a history of SARS-CoV-2 infection reported by the subject or legal representative is defined as having tested positive for SARS-CoV-2 infection (based on RT-PCR, other nucleic acid detection methods, or SARS-CoV-2 antigen test) in the past or having been diagnosed with COVID-19 based on a physician's medical examination in the past. Otherwise, the subject is defined as having no self-reported SARS-CoV-2 infection history.

- 3) The investigator, subinvestigator, or study staff will register the required subject information in the IRT based on the source documents for the subject who provided written informed consent and obtain the subject number.
- 4) The investigator or subinvestigator will prepare a subject screening list based on the subject number allocated by the IRT.
- 5) The investigator or subinvestigator will perform the following investigations,

Confidential

observations, and examinations, and confirm the subject's eligibility (based on the inclusion/exclusion criteria).

- Axillary body temperature (actual measured value)
- SARS-CoV-2 antigen test
- SARS-CoV-2 antibody test\* (measurement using a rapid test kit at the study site)
- Pregnancy test (urine)\*

\*1: If performed by venous blood, the sampling for clinical laboratory tests, immunogenicity evaluation and SARS-CoV-2 antibody test prescribed in Section 6.2 can be performed at the same time, taking into account the burden on the subject caused by blood sampling.

\*2: To be performed for women of childbearing potential only.

- 6) The investigator, subinvestigator or study staff will enter confirmation of the subject eligibility (based on the inclusion/exclusion criteria) in the IRT. If the subject dropped out when eligibility is evaluated, the date and the reason for dropout will be entered in the IRT.

#### Definition of History of SARS-CoV-2 Infection at Enrollment

A subject will be defined as having a history of SARS-CoV-2 infection at enrollment if he/she is determined to have a self-reported SARS-CoV-2 infection history or have a positive SARS-CoV-2 antibody with the rapid test kit at the time of eligibility evaluation. Otherwise, the subject will be defined as having no history of SARS-CoV-2 infection.

- 7) The IRT will randomize the eligible subject to an administration and notification of the assigned study drug will be sent to the unblinded personnel at the study site. The investigator, subinvestigator, or study staff will enter the randomization date in the eCRF.

## 6.2 Study Drug Administration (Day 1, No Allowance)

- 1) The investigator or subinvestigator will perform the following investigations, observations, and examinations, and document them in the eCRF. The result of determination of the subject's eligibility for study drug administration will be sent to unblinded personnel at the study site (study drug preparer and study drug administration personnel).
- Clinical laboratory tests (blood/urine)
  - Blood sampling for immunogenicity evaluation
  - SARS-CoV-2 antibody test (to be performed at the central laboratory)
  - Determination of the subject's eligibility for study drug administration specified in Section 5.6

Confidential

- 2) The unblinded personnel at the study site (study drug manager or study drug management assistant designated by the study drug manager) will confirm the assigned study drug based on the IRT notification. The assigned study drug will be dispensed in a separate location from the blinded personnel. The study drug preparer will prepare the injection syringe with the prescribed dose of the study drug.
- 3) The study drug administration personnel will administer the prepared study drug to the subject according to the study drug administration procedures and record the following items in the source document: the date of study drug administration, whether or not administration was completed, the administration site (right or left arm), and whether or not any dosing error occurred. If there was a dosing error, the subject number for which the study drug was actually administered will be identified and recorded. The investigator, subinvestigator, or study staff will enter the information recorded in the source document in the eCRF. The investigator or subinvestigator will monitor the subject's condition carefully for at least 30 minutes after study drug administration, and enter the results of the monitoring in the eCRF.
- 4) For the initial treatment in the event of an allergic reaction, the investigator, subinvestigator, or study staff will prepare the necessary drugs and equipment for emergency treatment. The investigator or subinvestigator will enter the treatments provided against all AEs in the eCRF.
- 5) The investigator, subinvestigator, or study staff will give a thermometer and the electronic diary (with instruction leaflets) to the subject or legal representative, and explain how to use them. An electronic diary entry device will also be given to them, if necessary.

### 6.3 Telephone Contact after Study Drug Administration (Day 8, Day 15, Day 22; Allowance $\pm$ 2 Days)

- 1) The investigator, subinvestigator, or study staff will contact the subject or legal representative by telephone on Day 8, Day 15, and Day 22, and ask about the subject's health status. Records of telephone contact documenting whether or not the contact was made and the date of the contact will be kept. It is also acceptable to ask the subject to return to the study site for health status confirmation.
- 2) Based on the record of telephone contact, the investigator, subinvestigator, or study staff will record whether or not the contact was made and the date of the contact in the eCRF.
- 3) The investigator or subinvestigator will judge if the subject's visit is necessary based on the information collected via telephone contact, and document the judgment in the source document.

#### 6.4 Post-dose Evaluation (Day 29, Allowance + 3 Days)

- 1) The subject will be requested to visit the study site for the post-dose evaluation at 4 weeks after study drug administration. The investigator or subinvestigator will confirm the subject's health status by medical interview and review the descriptions in the electronic diary to determine the seriousness, severity, and causality of nonserious unsolicited AEs, SAEs, and AEs leading to withdrawal from the study during the period from study drug administration to the study visit for the post-dose evaluation at 4 weeks after study drug administration in accordance with the definitions in Section 9.3, and record the results on the AE page of the eCRF. The use of concomitant medications/therapies during the period from study drug administration to the study visit for the post-dose evaluation at 4 weeks after study drug administration will also be confirmed.
- 2) The investigator or subinvestigator will perform the following investigations, observations, and examinations, and document them in the eCRF.
  - Blood sampling for immunogenicity evaluation
  - Clinical laboratory tests (blood/urine)
  - Pregnancy test (urine)\*
  - SARS-CoV-2 antibody test (to be performed at the central laboratory)
- 3) The investigator or subinvestigator will confirm that all data in the electronic diary have been transferred and then confirm that the application for data entry has been uninstalled from the electronic diary entry device. If a device has been lent to the subject or legal representative, the investigator or subinvestigator will collect the device.

\*: For women of childbearing potential only.

#### 6.5 Follow-up Examination (Day 57 [Allowance $\pm$ 7 Days], Day 85 [Allowance $\pm$ 7 Days], Day 113 [Allowance $\pm$ 7 Days], Day 141 [Allowance $\pm$ 7 Days], and Day 183 [Allowance $\pm$ 14 Days])

The subject will visit the study site on Day 57, Day 85, Day 113, Day 141, and Day 183. The investigator or subinvestigator will perform the following investigations, observations, and examinations, and document them in the eCRF. For subjects aged 12 to 17 years, only subjects who are able to visit the study site will visit the study site on Days 57, 113, and 141. In addition, if a solicited AE is ongoing at the study visit for the post-dose evaluation, the investigator or subinvestigator will confirm the outcome of the solicited AE, and enter the log number, event term and date of outcome of the event in the electronic diary in the eCRF.

- Blood sampling for immunogenicity evaluation
- SARS-CoV-2 antibody test (to be performed at the central laboratory)

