## 2.3.5 Safety Endpoints

- Solicited AEs (injection site and systemic) collected from the electronic diary within 7 days after study drug administration
- Unsolicited AEs within 28 days after study drug administration
- SAEs from the time of informed consent to 26 weeks after study drug administration
- Clinical laboratory values for 28 days after study drug administration

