## 6.13 Response in the Case of Suspected SARS-CoV-2 Infection

The investigator, subinvestigator, or study staff will explain to the subject and legal representative about symptoms suspected to indicate SARS-CoV-2 infection and instruct the legal representative to immediately contact the study site if the subject encounters such symptoms within 26 weeks (Day 183) after study drug administration or if the legal representative voluntarily determines that the subject may have been infected and the subject visits a medical institution providing COVID-19 treatment such as a fever outpatient clinic.

If the investigator or subinvestigator determines that the subject is suspected to have been infected with SARS-CoV-2 based on symptoms and the subject's status heard from the subject or legal representative via telephone, etc. (eg, the subject's cohabiting family member is found to have been infected with SARS-CoV-2 in the last few days, or a person involved in the environment around the subject such as school is found to have been infected with SARS-CoV-2), the subject or legal representative should be instructed to ensure that the subject will promptly visit the study site or a medical institution providing COVID-19 treatment such as a fever outpatient clinic. The investigator or subinvestigator will record the axillary body temperature measurement (actual measured value), the presence or absence of respiratory symptoms, malaise, headache, gastrointestinal symptoms, nasal discharge/nasal congestion, pharyngeal pain, dysgeusia, olfactory dysfunction, arthralgia, or myalgia, as well as the date of onset of symptoms, as obtained via telephone, etc., in the eCRF.

In the case of receiving treatment at the study site, nasopharyngeal swab samples for RT-PCR

testing will be collected to determine the presence or absence of SARS-CoV-2 infection. Detailed methods for sampling, collection, and testing procedures are specified in a separately prepared procedure manual. Leftover nasopharyngeal swab samples after RT-PCR testing may be used for future examinations. Details are specified in a separately prepared plan.

Blood sampling for immunogenicity evaluation will be performed whenever possible and the samples will be cryopreserved at  $\leq -70^{\circ}\text{C}$  after serum separation.

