#### 6.14 Response in the Case Where Cohabiting Family of Subject Is Determined to Be Infected with SARS-CoV-2

The investigator, subinvestigator, or study staff should instruct the subject or legal representative to immediately contact the study site if the subject's cohabiting family member has been diagnosed with SARS-CoV-2, for 26 weeks (Day 183) after study drug administration.

If the investigator, subinvestigator, or study staff obtains information that the subject's cohabiting family member has been diagnosed with SARS-CoV-2, the presence or absence of occurrence of symptoms suspected to indicate SARS-CoV-2 infection should be confirmed by telephone or other means. The investigator or subinvestigator will record the date that the subject's cohabiting family member was determined to have been infected with SARS-CoV-2 in the eCRF. If the subject is confirmed to have experienced symptoms suspected to indicate SARS-CoV-2 infection by telephone, etc., this should be handled in accordance with Section 6.13.

The investigator, subinvestigator, or study staff should instruct the subject or legal representative to immediately contact the study site if the subject has symptoms suspected to indicate SARS-CoV-2 infection after the date that the subject's cohabiting family member is judged to have been infected with SARS-CoV-2.

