### 9.2 Adverse Event Collection and Reporting

All SAEs (for the definition of SAEs, see 9.3.1 and 9.3.2) reported after the subject or legal representative signs the ICF until the study visit at 26 weeks after study drug administration (follow-up period), regardless of whether they are confirmed by the investigator or subinvestigator or reported by the subject or legal representative, will be recorded on the AE page of the eCRF. SAEs will be followed until the AE disappears, is stabilized, or is found not to be serious, or the subject is lost to follow-up.

Nonserious unsolicited AEs reported from study drug administration to the study visit at 4 weeks after study drug administration will be recorded on the AE page of the eCRF. Medical conditions that were diagnosed or known to exist before the first administration of the study drug (including clinically significant laboratory values/vital signs that are out of normal range but are not related to the underlying disease) will be recorded not on the AE page but as part of medical history or complications. For any medical occurrence ongoing on the date of the first administration of study drug, the eCRF "Medical History/Complications" module will record the start date of the medical occurrence even if the onset date is before the first administration of study drug. Worsening of preexisting medical occurrences or symptoms (excluding conditions related to the underlying disease), including worsening of severity after the first administration of the study drug, will be recorded on the AE page. SAEs will be reported according to the procedures specified in Section 9.6.

All clinical laboratory test results and vital signs will be evaluated and their clinical significance will be determined by the investigator or subinvestigator. Sporadic abnormalities of clinical laboratory test results and vital signs (ie, findings not consistent with part of reported diagnoses) will be reported as AEs if they are symptomatic, lead to permanent discontinuation of study treatment, require treatment for symptomatic relief, and are regarded as AEs based on the clinical judgment of the investigator or subinvestigator.

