The investigator or subinvestigator will confirm whether any AEs have occurred through medical interviews at study visits, subject's electronic diary, hearing of the subject's condition from the subject by telephone confirmation, etc., during the study, or medical examinations. AEs may be directly observed, reported spontaneously by the subject or legal representative, or found by medical interview at each study visit. The subject and legal representative should be questioned in a general way, without asking about the occurrence of any specific symptoms. The investigator or subinvestigator will evaluate nonserious unsolicited AEs, SAEs, and AEs leading to permanent

Confidential

discontinuation of study treatment or withdrawal from the study, and determine the seriousness, severity, and causality according to the definitions provided in Section 9.3. The evaluation by the investigator or subinvestigator will be clearly recorded in the source documents retained at the study site, with signature of the investigator or subinvestigator.

AEs should always be reported as a diagnosis. When a diagnosis is unavailable, the primary sign or symptom will be reported as the event term with additional details included in the narrative until the diagnosis becomes available. If the signs and symptoms are distinct and do not suggest a common diagnosis, they should be reported as individual entries of AEs.

For events that are serious due to hospitalization, the reason for hospitalization should be reported as SAE (diagnosis or symptom requiring hospitalization). Procedures (treatment and surgery) will not be handled as AEs, with no exception, but the reason for the procedure may be an AE. Pre-planned (before signing the ICF) procedures or treatments under hospitalization for preexisting medical conditions that do not worsen in severity need not be reported as SAEs (see Section 9.3.2 for definitions).

For deaths, after confirming the underlying or immediate cause of death, it should always be reported as an SAE.

Any serious, untoward event that may occur subsequently to the reporting period that the investigator or subinvestigator evaluates as related to the study drug should also be handled and reported as an SAE.

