### 11.4.2.2 Additional Secondary Efficacy Analysis

The incidence of COVID-19 (number of cases per 1000 person-years) for 4 weeks, 12 weeks, and 26 weeks after study drug administration will be calculated. The cumulative incidence will be calculated by administration arm using the Kaplan-Meier method.

The ratios of incidence (DS-5670d group vs. Comirnaty RTU IM group) and their 2-sided 95% confidence intervals will be calculated.

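### The Day 183 ± 14 visit window does not fit two rules that assume a fixed 26 weeks: the outside-vaccine ban can end before the 26-week sample, and SAE recording can stop before the SAE endpoint does

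*Protocol*

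**What the plan says.** Section 6.5 and Table 17.1-1 place the final visit, with its immunogenicity sample, at "Day 183 [Allowance $\pm$ 14 Days".

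**Vaccine ban.** Section 5.7.1 says that SARS-CoV-2 vaccines from outside the study "will be prohibited for 26 weeks after study drug administration because they may influence the evaluation of long-term efficacy and safety". Footnote c of Table 17.1-1 gives the same end point. Neither links the ban to the date of the last sample.

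**SAEs.** The endpoint in section 2.3.5 is "SAEs from the time of informed consent to 26 weeks after study drug administration", and the synopsis reports it as an incidence proportion. Section 9.2 defines collection differently: SAEs are recorded "until the study visit at 26 weeks after study drug administration (follow-up period"). After that, section 9.2 keeps one route open, "Any serious, untoward event that may occur subsequently to the reporting period", but only if the investigator judges the event related to study drug. Section 5.9 completes the study for the subject once the 26-week procedures and the follow-up of any persisting AE are done. Table 17.1-1 schedules no later contact.

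**Analysis.** Section 11.2 removes subjects from the per-protocol sets for significant violations and gives use of prohibited medication or therapy as an example. Sections 2.3.3 and 11.4.3 make the 26-week GMT and seroresponse rate exploratory. Section 5.7 requires concomitant medication to be recorded only up to the 4-week visit.

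**The concern.** A two-sided visit window is ordinary. The difficulty is that some rules follow the visit and others follow the calendar, so the two can part by up to two weeks in either direction.

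On the late side, the ban exists because another vaccine could disturb the long-term evaluation. If it lapses before the sample is drawn, it does not protect the last time point of that evaluation. Because the vaccination is permitted, the violation-based exclusion does not apply, and with recording required only to 4 weeks the database may not show that it happened. The 26-week GMT and seroresponse rate serve the exploratory objective on persistence (section 2.1.3), so each arm's own estimate matters as well as the contrast.

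On the early side, the SAE summary is a proportion with no time denominator. An early attender who has an unrelated SAE between the visit and Day 183 counts as event-free for a period that the endpoint claims to cover.

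**Working it through.** **1. The plan's own day count.** With dosing on Day 1, study day = 1 + 7 × weeks. For 26 weeks, 1 + 7 × 26 = 183, as stated. The same formula returns Days 29, 57, 85, 113 and 141 for weeks 4, 8, 12, 16 and 20.

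**2. Window limits (section 6.5).** Earliest: 183 − 14 = Day 169, which is 24.0 weeks. Latest: 183 + 14 = Day 197, which is 28.0 weeks.

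**3. Late side.** The ban covers 26 weeks, to Day 183. The first permitted day is Day 184 and the last permitted sample is on Day 197. The longest compliant interval from outside vaccine to sample is 197 − 184 = 13 days.

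If a share g of an arm were vaccinated in that gap and their titres had risen k-fold by sampling, the arm's GMT would be multiplied by k^g. The protocol gives neither g nor k, so these values are assumptions:
- g = 1%, k = 2: 2^0.01 = 1.007
- g = 2%, k = 3: 3^0.02 = 1.02
- g = 5%, k = 2: 2^0.05 = 1.035
- g = 10%, k = 2: 2^0.10 = 1.072

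**4. Early side.** A visit on Day 169 leaves Days 170 to 183 uncovered: 14 days out of 182, or 14/182 = 7.7% of the endpoint period for that subject. If a share f of the 690 planned subjects with prior infection or vaccination attended on Day 169, the person-time outside mandatory SAE collection would be 690 × f × 14 / 365.25:
- f = 10%: 2.6 person-years
- f = 25%: 6.6 person-years
- f = 50%: 13.2 person-years

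The shares are assumed. Only SAEs judged unrelated are at risk of being missed, since related ones remain reportable.

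**5. Combined reading.** For a visit on Day 169, an unrelated SAE on Day 175 is inside the endpoint of section 2.3.5 and outside the collection rule of section 9.2. For a visit on Day 197, a vaccine on Day 184 is allowed by section 5.7.1 and precedes the sample allowed by section 6.5. Both cases comply fully with the protocol.

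**The case against.** The strongest reply is that 26 weeks is nominal throughout: the synopsis describes the observation period as approximately 26 weeks, and some tolerance around a last visit is needed. The window is the same in both arms. SAE analysis is descriptive. Section 11.4.3 plans no between-arm test or margin at 26 weeks. Late visits lengthen SAE collection as early ones shorten it, so under an even spread of visits the mean collection time is still 26 weeks. Handling of post-vaccination samples and of follow-up time could also be settled in the SAP, which is not among the documents.

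Most of this stands, and it limits the severity. It does not remove the mismatch. An average of 26 weeks does not recover an unrelated SAE in an early attender, and an analysis rule cannot exclude samples taken after a vaccination that the protocol does not clearly require sites to record at that stage.

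Three stronger readings are not supported:

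- **Early visits cut short COVID-19 collection.** The text does not say so. Section 6.13 asks for symptom reports "within 26 weeks (Day 183) after study drug administration", and section 6.14 asks for household reports "for 26 weeks (Day 183) after study drug administration"; both are tied to the day and not to the visit. Section 11.4.2.2 plans "The incidence of COVID-19 (number of cases per 1000 person-years) for 4 weeks, 12 weeks, and 26 weeks" with Kaplan-Meier estimates, and these can accommodate shorter follow-up. At most, the end-of-study wording in section 5.9 leaves some ambiguity.
- **About 1.9% of all observation is lost.** That figure (0.5 × 7/182) counts early visits only, ignores the extension from late ones, and rests on an even spread that nothing in the protocol supports.
- **The 26-week GMT could be inflated by a quarter.** A factor of 10^0.10 = 1.26 needs 10% of all subjects vaccinated in the gap. If half the visits are late, that is about 20% of late attenders, each with a 10-fold rise completed within 13 days. The protocol offers no basis for such inputs.

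**Conclusion.** The point holds as two textual mismatches, and it is minor. A compliant outside vaccine can precede the 26-week sample by up to 13 days without triggering exclusion. Mandatory SAE recording can end up to 14 days (7.7%) before the endpoint period does, with only related events captured afterwards.

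The size of either effect is unknown, because it depends on when subjects attend and whether they seek another vaccine, and the protocol gives no figures for these. The illustrations with modest assumed inputs are small. The primary and key secondary endpoints at 4 weeks are not affected; what is affected is an exploratory titre summary and a descriptive safety proportion. The conclusion itself rests only on the stated days and windows.

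**What to change.** **Vaccine ban and sample.** Reconcile the end of the prohibition in section 5.7.1 and Table 17.1-1 footnote c with the sampling window in section 6.5; which rule governs is for the sponsor to decide. Ask about outside SARS-CoV-2 vaccination, with its date, at the 26-week visit. Exclude from the 26-week GMT and seroresponse rate any sample drawn after such a vaccination.

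**SAE period.** Align section 9.2 with section 2.3.5, either by collecting SAEs to the later of Day 183 and the 26-week visit, with a brief call for those seen early, or by reporting SAE rates by each subject's actual follow-up time. The first option brings the gap for early attenders to 0 days. The second leaves collection as it is and makes the denominator honest.

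**Cost.** A few lines of protocol text, one question at the last visit, a short call for some subjects if the first SAE option is taken, and possibly a few samples dropped from an exploratory summary.
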